#### Process evaluation

Formal mediation analyses will be conducted to identify the mechanisms by which the self-regulation intervention may work. If no clustering effects are found, the bootstrapping approach recommended by Preacher and Hayes will be used [35]. However, if clustering effects are present, then the Preacher and Hayes method would underestimate standard errors, so the Sobel [36] method will be used, with standard errors derived from the mixed effects model. In both instances, changes in TPB variables over the course of the intervention sessions (i.e. between t1 and t2) will be examined as potential mediators of effects on behaviour at t2. Changes in TPB variables over the course of the entire follow-up period (i.e. between t1 and t4) will be examined as potential mediators of effects on behaviour at t4.

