**Figure 1 F1:**
[figure not shown]
**Flowchart showing planned study recruitment numbers, and timing of intervention sessions and measurements**.

For patients in practices allocated to the information provision control condition, the session will continue with delivery of the "information provision" intervention as described above: the PN/HCA will provide their patients with an information pack of materials promoting walking, and answer any questions the patient may have about walking more. At the end of this session, patients complete the post-intervention (t2) questionnaire, consisting of the brief TPB measure only, and are given a pedometer, with detailed instructions in its use. They are asked to wear it for a week, and return to the research team in a reply-paid envelope. This forms the first post-intervention assessment of walking.

For patients in practices allocated to the self-regulation intervention condition, the PN/HCA provides their patients with an information pack of materials promoting walking, and answers any questions the patient may have about walking more. Following this, two further face-to-face appointments will be booked, for delivery of the self-regulation intervention (as described above), at one week and two weeks after this initial session, plus the final intervention session four weeks after the initial session. At the end of this session, patients are given a pedometer, with detailed instructions for its use. They are asked to wear it for a week, and return it at their first intervention session where the PN/HCA will extract the data from the pedometer. This initial assessment of walking constitutes a pre-intervention measurement for those patients in the intervention arm.

Patients in practices allocated to the intervention condition then receive the self-regulation intervention, as detailed above. Sessions one and two will be tape-recorded, with the explicit agreement and signed consent of the patients involved. At the end of the second face-to-face session, patients complete the post-intervention (t2) questionnaire, and are given a pedometer, to wear for a week, and then return to the research team in a reply-paid envelope. This forms the first post-intervention assessment of walking.

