Patients in practices allocated to the intervention condition receive a final follow-up intervention session, which may be by telephone or face-to-face, two weeks after their second face-to-face session. Despite this, the measurement procedures for patients in practices in both conditions are identical from t2 onwards.

At six weeks post intervention (i.e. six weeks after t2 for both groups), all patients are sent a questionnaire by post (t3) containing the brief TPB measure, and a pedometer, and asked to return these by post. At six months post intervention (t4), all patients are sent a questionnaire containing a full TPB measure, the EQ5D, and a final pedometer, which again they are asked to return by post.

To encourage retention, all participants who complete and return questionnaires or pedometers from t2 onwards will be sent postal feedback on their walking behaviour and psychological measurements in the form of a postal profile. Those who do not send back the pedometer at any measurement point will receive a reminder letter and follow-up telephone calls from the research team encouraging them to return these, as loss of numerous pedometers will be expensive, and threaten the validity of the study.

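### The mediation analysis drops the practice effect whenever clustering is not detected, and at six months it cannot show which came first, the change in beliefs or the walking

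*Protocol article*

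**What the plan says.** **Choice of method.** The Process evaluation section of the protocol article sets a conditional rule. The first branch reads: "If no clustering effects are found, the bootstrapping approach recommended by" the cited authors is used. For the other branch, the section says that this bootstrap "method would underestimate standard errors, so the Sobel [36] method will be used, with standard errors derived from the mixed effects model". It names no test, threshold or variable for deciding whether clustering is there. By contrast, the Analysis section fits a random practice effect in the main comparison without any condition, the Practice randomisation section allocates whole practices, and the Sample size section assumes an ICC of 0.010.

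**Timing of mediator and outcome.** For the first post-intervention assessment, changes in the Theory of Planned Behaviour (TPB) variables ("i.e. between t1 and t2) will be examined as potential mediators of effects on behaviour at t2") are used. The section on consent, receipt of intervention and follow-up gives the order there: "patients complete the post-intervention (t2) questionnaire, and are given a pedometer, to wear for a week". For six months the rule is the change ("i.e. between t1 and t4) will be examined as potential mediators of effects on behaviour at t4"), and the data arrive together: "all patients are sent a questionnaire containing a full TPB measure, the EQ5D, and a final pedometer". No order of completion is stated. An intermediate reading exists in both arms, because at six weeks "all patients are sent a questionnaire by post (t3) containing the brief TPB measure".

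**The concern.** Arm is constant within a practice, so the arm-to-mediator path is a between-practice contrast whatever a test of clustering shows. Failing to detect a practice effect with 20 practices is weak evidence that there is none. The rule therefore sends many trials with real clustering to the method that the plan concedes is too precise. The other branch, Sobel, treats a product of two coefficients as normally distributed, so the two branches also differ in more than their handling of practice.

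At t4 the belief score and the walking reading share a mailing. A patient who completes the questionnaire after the pedometer week may report more confidence because of having walked more.

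Identifying mechanisms is aim (b) of the trial, and the Conclusion section looks to the mediation analyses, together with the pilot fidelity work, to explain a null result. What is at stake is the reliability of those mechanism statements.

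**Working it through.** **Inputs from the Sample size section:** 20 practices (10 per arm), 20 patients each, SD 15 minutes/day, ICC 0.010, difference 5 minutes/day, stated power 85%. **Assumed:** two-sided 5% level; a 5% F test for a practice effect as the meaning of clustering being found; ICCs of 0.03 and 0.05 as a range, since no mediator ICC is given.

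**1. The plan's own figure.** Design effect = 1 + 19 × 0.010 = 1.19. Effective n per arm = 200/1.19 = 168.1. SE = 15 × √(2/168.1) = 1.636. Power = Φ(5/1.636 − 1.96) = Φ(1.096) = 86.3%, which agrees with the stated 85% to within 2 points. The inputs are read correctly.

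**2. How often clustering is missed.** With 18 and 380 degrees of freedom, power = P(F > Fcrit/λ), where λ = 1 + 20 × ICC/(1 − ICC). At ICC 0.010, λ = 1.202 and power is 15%, so 85% of trials miss it.

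**3. What a miss costs on the arm-to-mediator path.** The single-level SE is 1/√(design effect) of the true SE. At ICC 0.010 this is 1/√1.19 = 0.917, and type I error is 2 × [1 − Φ(1.96 × 0.917)] = 7.2%.

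**4. The whole rule.** Trials were simulated with no true arm effect on the mediator, pre-tested, then analysed by the single-level or the practice-level test as the rule directs. Ranges are over repeat runs.

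| ICC | Design effect | Single-level SE / true SE | Clustering missed | Error when missed | Error under the two-step rule | Error, practice always modelled |
|---|---|---|---|---|---|---|
| 0.010 | 1.19 | 0.92 | 85% | 7.3% | 6.3-6.4% | 5.0% |
| 0.03 | 1.57 | 0.80 | 55% | 11.9% | 7.4-7.8% | 5.0% |
| 0.05 | 1.95 | 0.72 | 29-30% | 16.6% | 6.8-7.4% | 5.1% |

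The two-step error stays moderate because the test misses clustering less often as the damage from a miss grows. The missed branch contributes 0.85 × 7.3% = 6.2 points at ICC 0.010, 0.55 × 11.9% = 6.5 at 0.03 and 0.29 × 16.6% = 4.8 at 0.05. The last column uses a t reference with 20 − 2 = 18 degrees of freedom.

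**5. The whole indirect effect.** A mediation claim also needs the mediator-to-walking path. With that path set at 0.1 to 0.4 (assumed), the two-step rule gave false-positive rates of 3.4-6.3% at ICC 0.01, 3.7-7.6% at 0.03 and 2.5-7.5% at 0.05. Across the checks, the rate is about 7-8% at most with a strong second path and below 5% with a weak one.

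**6. Direction at t4.** Suppose confidence only follows walking: M = rY + e in standardised units, with total arm effect c on walking. Then a = r × c and b = r, so the apparent mediated share is ab/c = r². For r = 0.3 to 0.5 (assumed) that is 9% to 25%, with no true mediation. If c = 0, then a = 0 and the spurious indirect effect is zero.

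**The case against.** **The criterion is not stated.** The article names no significance test, and a fuller plan may define one. If an ICC estimate above zero counted as clustering, it would be missed in about 34% of trials at ICC 0.010 (1 − 0.662), 11% at 0.03 and 4% at 0.05. That stands as a limit on the 85%. It does not remove the defect, because the conditional rule is itself stated.

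**The inflation is modest.** This stands. A reader might infer that mediation claims carry error rates of 12-17%. Those figures apply to the arm-to-mediator path in trials where clustering was missed, not to the rule as a whole. Nor does everything reported have understated errors: Sobel with mixed-model standard errors is, in general, conservative.

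**Direction is partly handled.** This also stands. In the t1-t2 analysis the questionnaire precedes the pedometer week, and the Outcome measures section frames the long TPB items around the coming seven days. But no t4 completion order is fixed, and postal feedback on walking from t2 onwards gives walking a route to later scores.

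**Reverse causation spoiling the explanation of a null result.** A reader might infer this from the Conclusion section. Step 6 shows otherwise: with no effect on walking, no spurious mediated effect is expected.

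**An earlier mediator is no clean substitute.** Baseline uses the 26-item form and t3 the 6-item form; only t1-t4 has the full form at both ends and covers control beliefs. A t3 score also follows earlier walking. That is why an earlier mediator should be added and should not replace t1-t4.

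**Conclusion.** The point holds at moderate size. Making the practice effect conditional on detection is wrong for a practice-randomised contrast, and it departs from the plan's own main analysis. At the protocol's ICC, type I error on the arm-to-mediator path rises from about 5% to about 6.4%, and at assumed ICCs of 0.03-0.05 to 7-8%. For the whole indirect effect the excess is small and disappears when the second path is weak. These figures rest on a 5% F test and full practices of 20. With 16 per practice (assumed), clustering is missed more often, in about 87%, 65% and 41% of trials, and the two-step error is 6.0-7.3%.

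The t4 ordering gap is real but conditional: it limits what can be said about direction only if the intervention changes walking. The size of any spurious share depends on an assumed correlation. This is a secondary process analysis, and nothing here touches the primary comparison of walking.

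**What to change.** 1. Delete the condition. Fit the mixed model with a random practice effect for both the arm-to-mediator and mediator-to-walking paths in every mediation analysis.
2. Replace Sobel and the single-level bootstrap with one interval for the indirect effect: Monte Carlo (distribution of the product) or a bootstrap that resamples whole practices. For the Monte Carlo version, draw the arm-to-mediator path from a t distribution with 18 degrees of freedom, because normal quantiles are too narrow with 20 practices.
3. Add a line to the t4 cover sheet asking patients to complete the questionnaire before they start wearing the pedometer.
4. Add an analysis of t4 walking on an earlier TPB change (t1-t2 or t1-t3) for the four constructs on the brief form, scored on items common to both forms once that overlap is confirmed. Keep the t1-t4 analysis and describe its result as association.

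The cost is a change of analysis wording and one line of patient instruction, with no new data. Intervals will be slightly wider. The added analysis does not cover control beliefs, and it improves time order without removing all confounding by earlier walking.

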## Methods/Design

### Study Design

This explanatory trial is a two-arm cluster randomised controlled trial, with clustering by GP practice. It will assess differences in objectively assessed walking between patients who receive a brief self-regulation intervention, compared with patients who are provided with information about the benefits of walking. PNs/ HCAs randomised to the intervention group will deliver a brief self-regulation intervention to eligible patients, targeting self-efficacy and planning. PNs/ HCAs randomised to the "information provision" control group will provide information to eligible patients using materials which are currently widely available.

The study protocol was approved by Birmingham East, North and Solihull Research Ethics Committee (REC Ref: 09/H1206/116).

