### Sample size

A total of 400 patients will be recruited from 20 PNs/HCAs (10 in each trial arm), each delivering the walking intervention sessions to 20 patients. Assuming a standard deviation of walking of 15 minutes/day, as obtained in a previous study with adult volunteers [14] and an intraclass correlation coefficient of 0.010, equal to the median value found in a review of clustering effects in practices in primary care [26], this will provide 85% power to detect a mean difference of five minutes/day walking between the intervention group, and the control group.

The difference in walking between groups that this explanatory trial is powered to detect is smaller than that observed in a previous study with adult volunteers [14] (12.4 mins/day over the first week, Cohen's d = 0.90) due to participants being primary care patients rather than volunteers, there being lower anticipated fidelity of treatment delivery, and a longer duration of outcome follow up.

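### The mediation analysis drops practice clustering whenever none is "found", although practices are the randomised unit; the likely error is modest, and practice should be accounted for in every mediation model.

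*Protocol article*

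**What the plan says.** The Process evaluation section sets a two-branch rule. The first branch reads "If no clustering effects are found, the bootstrapping approach recommended by" its named authors will be used. The second reads "if clustering effects are present, then the Preacher and Hayes method would underestimate standard errors, so the Sobel" method follows, with standard errors taken from the mixed effects model. No test, significance level or ICC threshold defines when clustering counts as found. The candidate mediators are changes in Theory of Planned Behaviour (TPB) scores from t1 to t2 and from t1 to t4.

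Elsewhere the article treats clustering as given. Study Design describes a "two-arm cluster randomised controlled trial, with clustering by GP practice". Practice randomisation allocates arms by practice. Sample size uses "an intraclass correlation coefficient of 0.010, equal to the median value found in a review of clustering effects in practices in primary care". The Analysis section fits a random practice effect to walking without any preliminary check.

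**The concern.** Arms are assigned by practice, so the effect of arm on a mediator is a comparison between practices, whether or not a between-practice variance shows up in the data. The rule moves from clustering not being found to clustering not being present. With 20 practices those are different things. When the first branch is taken by mistake, the method used is the one that the protocol says is too optimistic.

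Identifying mechanisms is aim (b) of the trial. The Conclusion section also relies on the mediation analyses to explain a null result, in particular to tell an intervention that did not move the mediators from one that moved them without changing walking. That distinction turns on the arm-to-mediator path, which is where the standard error would be too small.

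**Working it through.** **Inputs.** The sample-size section gives "A total of 400 patients will be recruited from 20 PNs/HCAs (10 in each trial arm), each delivering the walking intervention sessions to 20 patients", so k = 20 clusters, m = 20 and 200 patients per arm; ICC ρ = 0.010; SD 15 minutes/day; difference 5 minutes/day. Assumed: one deliverer per practice, complete balanced data, two-sided 5% level, and the same ρ for the mediators as for walking.

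**1. The plan's own figure.** Design effect = 1 + (20 − 1) × 0.010 = 1.19. Effective n per arm = 200/1.19 = 168.1. SE = 15 × √(2/168.1) = 1.636. Power = Φ(5/1.636 − 1.96) = Φ(1.096) = 86.3%, close to the stated 85% (82.4% with a t reference on 18 df). The inputs are therefore read as the plan intended.

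**2. Chance of missing clustering at ρ = 0.010.** The within-arm F statistic for practice has 20 − 2 = 18 and 20 × 19 = 380 df. Its expected mean squares are in the ratio 1 + mρ/(1 − ρ) = 1 + 0.20/0.99 = 1.202.
- 5% test: critical value 1.631; P[F < 1.631/1.202 = 1.357] = 85%.
- 10% test: 76%.
- 20% test: critical value 1.276; P[F < 1.276/1.202 = 1.061] = 61%.
- REML likelihood-ratio test at 5%: 87% with the boundary mixture, 92% with plain chi-square on 1 df.
- Estimated variance above zero: P[F < 1/1.202 = 0.832] = 34%.

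With 16 or 14 analysed patients per practice, the 5% F test misses clustering 87.5% or 88.7% of the time.

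**3. Cost when it is missed.** The true SE of the arm contrast is √1.19 = 1.09 times the SE that ignores practice. A nominal 5% test then has error 2 × [1 − Φ(1.96/1.091)] = 7.2%.

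**4. The whole two-step procedure for the arm-to-mediator path.** This was simulated from balanced mean squares with no true arm effect and 2 million draws per ICC. The pre-test is the 5% F test. The ranges reflect a t (18 df) or a normal reference in the mixed-model branch.

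| ICC | Clustering missed | Error when missed | Error of whole procedure |
|---|---|---|---|
| 0.010 | 85% | 7.2% | 6.3–6.4% |
| 0.02 | 71% | 9.6% | 7.2–7.4% |
| 0.03 | 55% | 12.0% | 7.5–7.9% |
| 0.05 | 29% | 16.5% | 6.9–7.8% |

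Always using the between-practice mean square with t on 18 df gives 5.0% throughout. At ICC 0.010, a 20% pre-test brings the procedure to 5.1–5.5%, and the above-zero rule to 4.3–5.1%.

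**5. The indirect effect.** This was simulated with no arm-to-mediator effect and the 5% pre-test, using Monte Carlo intervals in place of the bootstrap (6,000 trials per cell). For standardised mediator-to-walking slopes of 0.1, 0.2 and 0.4, the error is 2.4%, 6.1% and 6.3% at ICC 0.010, and 2.2%, 5.5% and 6.9% at ICC 0.05. The inflation reaches the indirect effect only when the second path is reasonably strong.

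**The case against.** The strongest reply is that the protocol never says that clustering is found by a 5% test. The mixed model is fitted anyway, so a non-zero estimated practice variance is an equally natural reading. Under that reading the naive method is chosen about a third of the time at ICC 0.010, and the inflation largely or wholly goes. The exact criterion may also sit in an analysis plan that is not shown. This stands: the 85% figure belongs to one reading of the rule and cannot be offered as what would usually happen.

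Three further objections also stand. The 0.010 is a planning value for walking, and no ICC for TPB change scores is given. The error rates of 12.0% and 16.5% are conditional on missing clustering at ICCs three and five times the planning value, and at 0.05 that happens in only 29% of trials. Finally, this is a process evaluation, and the walking comparison always carries the practice effect.

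A reader might infer that different mediators or time points would be switched between methods by chance. The text does not say that the choice is made separately for each, and it applies the same mediators and time points to both methods, so this is conjecture.

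The objection does not rescue the rule itself. A branch that ignores the randomised unit has no justification from the design, and the article gives no advantage for keeping it.

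**Conclusion.** The conditional rule is wrong as written, because it lets non-detection stand in for absence of clustering in a practice-randomised trial, against the article's own sample-size assumption and its own walking analysis. The consequence is modest. At ICC 0.010 and with a 5% pre-test, the arm-to-mediator test runs at about 6.4% instead of 5%, rising to about 7 to 8% at ICCs of 0.02 to 0.05. This rests on two assumptions that the documents do not settle: that clustering is judged by a significance test, and that the mediators have an ICC in this range.

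It would go too far to conclude that aim (b) would rest on intervals that are too narrow in most realisations. That depends on the unstated criterion, and with a weak mediator-to-walking path the test of the indirect effect is conservative. The walking comparison is unaffected. The change is worth making because it costs almost nothing.

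**What to change.** In Process evaluation, delete the conditional rule and state that every mediation model accounts for practice whatever the estimated ICC, using the same random practice effect as the walking analysis. Use between-practice degrees of freedom for the arm-to-mediator path: 18 with 20 practices, or 20 − 2 − 2 = 16 if practice size and deprivation are both in the model.

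Say how the indirect effect is tested: either from the mixed-model paths and their standard errors, or with a bootstrap that resamples whole practices within arm, not patients. If the bootstrap is chosen, note that plain resampling of 10 practices per arm scales the between-practice variance by 9/10, and so the SE by √0.9 = 0.95; a small-sample correction should be named.

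The cost is one sentence and slightly wider intervals. No new data are needed.

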#### Patient consent, receipt of intervention, and follow-up measurements

For both experimental conditions, each patient attends a face-to-face session at their own practice with the PN/HCA who is delivering the session. During this session, they are screened for whether they already do more than 30 minutes of moderate or vigorous physical activity per day on at least 5 days a week. If they are not already achieving this recommended level of physical activity, they are asked to provide informed consent, and complete the baseline (t1) questionnaire, which includes the full TPB measure, the EQ5D, and measures of ethnicity, employment status and education level. Information on patient date of birth, gender, and the clinical condition for which they were flagged (e.g. diabetes, hypertension, etc) will be recorded on a standardised form by PN/HCAs. The form will be sent to the research team, along with their contact details. Weight and height information for each patient will be recorded by the PN/HCA at baseline, which will allow calculation of body mass index. After this point, the procedure differs for patients in practices allocated to the self-regulation intervention condition, and patients in practices allocated to the information provision condition (see Figure 1).

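### The t1-to-t2 change in TPB scores, used as a mediator, spans one sitting in the control arm but about two weeks and a pedometer week in the intervention arm

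*Protocol article*

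**What the plan says.** For walking at t2, the Process evaluation section takes as mediator the TPB change between t1 and t2: "changes in TPB variables over the course of the intervention sessions (i.e. between t1 and t2) will be examined as potential mediators". A second analysis uses the change between t1 and t4 for behaviour at t4. The stated purpose is to find the mechanisms of the self-regulation intervention. No adjustment or caveat for timing is given.

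The timing is set out under Patient consent, receipt of intervention, and follow-up measurements:

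- **Both arms.** At the initial session, patients "complete the baseline (t1) questionnaire, which includes the full TPB measure, the EQ5D" and other items.
- **Control.** The same appointment carries on with the information pack. "At the end of this session, patients complete the post-intervention (t2) questionnaire, consisting of the brief TPB measure only". The first pedometer is handed over only then.
- **Intervention.** Patients leave the initial session with the pack and a pedometer, wear it for a week and return it at session one. The protocol calls this week's reading a pre-intervention measurement. The later contacts are "at one week and two weeks after this initial session, plus the final intervention session four weeks after the initial session". On the timing of t2 the text reads: "At the end of the second face-to-face session, patients complete the post-intervention (t2) questionnaire".
- **After t2.** Intervention patients "receive a final follow-up intervention session, which may be by telephone or face-to-face, two weeks after their second face-to-face session". The protocol describes measurement procedures as identical in the two arms from t2 onwards. It makes no such statement for t1 to t2.

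**The concern.** A mediation analysis needs the arm effect on the mediator to represent the intervention whose mechanism is being sought. Randomising practices makes the arm difference in t1-to-t2 change a valid total effect of everything that differs between arms in that window. Here that includes more than the sessions: two weeks of elapsed time against none, a week of pedometer self-monitoring in one arm only, and a control group that answers the TPB items twice in one sitting. If the brief form keeps the seven-day horizon stated for the long form, control patients also rate the same coming week twice, while intervention patients rate two different weeks.

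Identifying mechanisms is aim (b) of the trial, and the Conclusion relies partly on mediation to explain a null result. A t1-to-t2 mediated effect could be reported as evidence about self-efficacy and planning techniques when part of it comes from timing and pedometer wear. The wording of the analysis section adds to this by presenting the window as the course of the sessions.

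**Working it through.** The document gives no figure for this point (no TPB means, changes or reliabilities). Its 85% power statement concerns walking and plays no part. The check is therefore a reconstruction of the schedule, with the initial session as day 0.

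**Dating t2 in the intervention arm.** Sessions one and two fall one and two weeks after the initial session, at days 7 and 14. As a cross-check, the final session is four weeks after the initial session (day 28) and "two weeks after their second face-to-face session", so session two is at 28 − 14 = day 14. Since t2 is completed at the end of session two, t2 is at day 14.

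| | Control | Intervention |
|---|---|---|
| t1 | day 0 | day 0 |
| t2 | day 0, same sitting | day 14 |
| t1-to-t2 interval | 0 days | 14 days |
| Pedometer weeks between t1 and t2 | 0 | 1 (days 0 to 7) |
| Week between sessions one and two, inside t1-to-t2 | none | days 7 to 14 |
| Pedometer week giving walking at t2 | days 0 to 7 | days 14 to 21 |
| Sessions still to come after t2 | none | one, at day 28 (28 − 14 = 14 days after t2) |
| t3 (t2 + 6 weeks) | 6 weeks after t1 | 6 + 2 = 8 weeks after t1 |
| Pedometer wears before t3 | 1 | 2 |
| t4 (t2 + 6 months) | 6 months after t1 | 6 months + 2 weeks after t1 |

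**What the arm difference contains.** Write the arm difference in t1-to-t2 change as a = a_S + a_O. Here a_S is the part due to the sessions, including the planned walking between them, and a_O is the part due to elapsed time, re-measurement and the pedometer week. With b the path from mediator to walking, the analysis reports a × b, while the quantity of interest is a_S × b. If a_O is a share s of a, then

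(a × b) / (a_S × b) = 1 / (1 − s).

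The document gives no value for s. Purely as assumptions, with b held fixed:

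- s = 0.10: 1 / 0.90 = 1.11
- s = 0.25: 1 / 0.75 = 1.33
- s = 0.50: 1 / 0.50 = 2.0

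The direction is not fixed either: if time or pedometer wear lowered scores, s would be negative and the ratio below 1.

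**Comparing the planned analyses.** The t1-to-t4 windows differ by two weeks in about six months, so that analysis is little affected by the gap. However, the t4 questionnaire and t4 pedometer are sent together, so its mediator is not clearly measured before its outcome. The t1-to-t2 analysis has the better order, because the questionnaire comes before the pedometer week, but it has the unequal window. A t3 score paired with t4 walking avoids most of both problems.

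**The case against.** Several stronger readings are tempting, and the document does not support them.

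- **That t2 self-efficacy is a result of walking and not its cause.** The t2 questionnaire is completed before the pedometer week that supplies the t2 outcome, so the measured outcome cannot have produced the score. Earlier walking may influence both. However, the Background names mastery experience as a likely route to self-efficacy, and session two is built around reviewing progress since session one. The week between those sessions is thus arguably part of the intervention, and it is not counted here as contamination.
- **That only intervention patients answer under the eye of their provider.** Control patients also complete t2 at the end of a practice session with the PN/HCA who delivered it.
- **That recall holds control change near zero.** This is plausible, but nothing in the document shows it.
- **That the size can be derived from test-retest correlations.** Any such correlations would be assumed, and unequal spread of change scores is not bias in the mean difference.
- **That aim (b) as a whole fails.** The t1-to-t4 analysis is largely untouched, and the explanation of a null result also draws on the fidelity work in the pilot.

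It can also be said that t2 follows both main sessions and that the later contact is a shortened repeat of session two. That makes the wording error small, but it remains an error. What the objection leaves standing is the unequal interval, same-sitting re-measurement in control, and a pedometer week that the protocol itself places before the intervention.

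**Conclusion.** The point holds in a limited form. The t1-to-t2 TPB change covers 0 days in control and 14 days in the intervention arm, with one pedometer week in the latter only. Its arm difference therefore cannot be read as the effect of the self-regulation sessions. It is the effect of the sessions together with elapsed time, re-measurement and self-monitoring. The schedule facts come directly from the text. That these factors move TPB scores is a reasonable expectation, but its amount is unknown, and the ratios of 1.11 to 2.0 illustrate assumed shares only.

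The effect is confined to one of two planned mediation analyses. The primary comparison of walking and the sample size do not depend on it, and the t1-to-t4 mediation is largely unaffected. It is worth correcting because mechanism is a stated aim and the remedy uses data already planned.

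**What to change.** In Process evaluation:

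1. Add a mediation analysis with the t3 brief TPB score (intentions, self-efficacy/PBC, attitudes, subjective norms) as mediator of walking at t4, adjusted for the t1 score on the same construct. The t3 measure is collected by post under the same procedures in both arms, after all sessions have ended, and it precedes the t4 outcome. The outcome should be named as t4: a t3 mediator would follow t2 walking, and the t3 questionnaire is sent together with the t3 pedometer.
2. Keep the t1-to-t2 analysis as exploratory. State that it describes the whole package, including pedometer wear and elapsed time, and not a technique-specific mechanism.
3. Reword the sentence that equates t1-to-t2 with the course of the intervention sessions, since the final session comes two weeks after t2.

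The cost is analysis wording only; no new data are needed. The downsides are:

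- non-response at t3;
- a weaker claim about mediation at t2;
- a remaining imbalance of about 8 against 6 weeks since t1, and one extra pedometer wear in the intervention arm;
- possible influence on t3 answers of the postal feedback sent after t2.

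The t3 score also follows some weeks of walking, so earlier behaviour may still drive both it and t4 walking. The report should say so.
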